# Study protocol ROTATE-trial: anterior cruciate ligament rupture, the influence of a treatment algorithm and shared decision making on clinical outcome– a cluster randomized controlled trial

**DOI:** 10.1186/s12891-021-04867-5

**Published:** 2022-02-05

**Keywords:** Anterior cruciate ligament rupture, Treatment algorithm, Shared decision making, Cost-effectiveness

## Abstract

**Background:**

Anterior cruciate ligament (ACL) rupture is a very common knee injury in the sport active population. There is much debate on which treatment (operative or non-operative) is best for the individual patient. In order to give a more personalized recommendation we aim to evaluate the effectiveness and cost-effectiveness of a treatment algorithm for patients with a complete primary ACL rupture.

**Methods:**

The ROTATE-trial is a multicenter, open-labeled cluster randomized controlled trial with superiority design. Randomization will take place on hospital level (*n* = 10). Patients must meet all the following criteria: aged 18 year or older, with a complete primary ACL rupture (confirmed by MRI and physical examination) and maximum of 6 weeks of non-operative treatment. Exclusion criteria consists of multi ligament trauma indicated for surgical intervention, presence of another disorder that affects the activity level of the lower limb, pregnancy, and insufficient command of the Dutch language. The intervention to be investigated will be an adjusted treatment decision strategy, including an advice from our treatment algorithm. Patient reported outcomes will be conducted at baseline, 3, 6, 12 and 24 months. Physical examination of the knee at baseline, 12 and 24 months. Primary outcome will be function of the knee measured by the International Knee Documentation Committee (IKDC) questionnaire. Secondary outcomes are, among others, the Tegner activity score, the Knee injury and Osteoarthritis Outcome Score (KOOS) and the 9-item Shared Decision Making Questionnaire (SDM-Q-9). Healthcare use, productivity and satisfaction with ((non-)operative) care are also measured by means of questionnaires. In total 230 patients will be included, resulting in 23 patients per hospital.

**Discussion:**

The ROTATE study aims to evaluate the effectiveness and cost-effectiveness of a treatment algorithm for patients with a complete primary ACL rupture compared to current used treatment strategy. Using a treatment algorithm might give the much-wanted personalized treatment recommendation.

**Trial registration:**

This study is approved by the Medical Research Ethics Committee of Erasmus Medical Center in Rotterdam and prospectively registered at the Dutch Trial Registry on May 13th, 2020. Registration number: NL8637.

## Background

Anterior cruciate ligament (ACL) rupture is a very common knee injury in the sport active population and has been well researched over the years. There is much debate on which treatment is best for the individual patient. We describe two treatments for an ACL rupture, namely anterior cruciate ligament reconstruction (ACLR) (operative treatment) and an intensive rehabilitation program (non-operative treatment). The primary goal of both treatments is to prevent instability of the knee joint. If treated non-operatively, the patient is guided through a rehabilitation program. If treated operatively, the patient receives a reconstructed ACL.

Two large multi-center randomized controlled trials, the COMPARE-study and the KANON-study, conclude that early (within 6 weeks of trauma) operative treatment of an ACL rupture is not superior to non-operative treatment plus optional delayed (after 3 months of trauma) ACLR [1, 2]. Half of the patients from both trials treated initially non-operatively were reconstructed during the 2 years follow-up. This means that this group eventually had two rehabilitation periods, namely one prior and one after the ACLR. It also suggests that half of the patients treated initially operatively, might not need surgical intervention. In the cost-effectiveness analysis of the COMPARE study, we reported that patients treated with rehabilitation and optional delayed ACLR have the lowest gain in quality of life and highest costs compared to patients treated with rehabilitation alone [3]. Segregation of patients at an early stage that perform well with non-operative treatment from those who do not, might influence the gain in quality of life and decrease costs on public healthcare by decreasing the proportion of patients who have two rehabilitation periods. Current practice is that treatment recommendation is based on expert opinion, taking into account patient characteristics and preferences (e.g. operative treatment because of an active sporting career) [4]. To give an appropriate and patient tailored answer to the question what to do with a patient with an ACL injury on individual level, we constructed a treatment algorithm to be used in the shared decision making process between physician and patient.

Treatment algorithms are nowadays widely used throughout medical healthcare [5]. The advantage of algorithms is the ability to analyze diverse data types (demographic data, laboratory findings, imaging data, and doctors’ free-text notes) and incorporate them into predictions for disease risk, diagnosis, prognosis, and appropriate treatments on an individual level [5]. Using a treatment algorithm for patients with ACL injuries might give the much-wanted personalized treatment recommendation and enables identification of the group of patients who perform poorly despite (non-)operative treatment.

In the decision-making process, scientific evidence, clinical expert opinion, and patient values or preferences come together to reach a shared decision about rehabilitation or surgery. There are some tools, such as decision aids or consultation cards that aim to facilitate this process [6]. Using a treatment algorithm might improve the perceived shared decision making, because the recommendations become more personalized. The effect of treatment algorithms and shared decision making on functional outcome of the knee after ACL rupture, to our knowledge, has not yet been researched.

This research topic was prioritized within the research agenda of the Dutch Orthopaedic Association (NOV).

## Methods

This manuscript is written according to the Consolidated Standards for Reporting Trials (CONSORT statement) and Standard Protocol Items: Recommendations for Interventional Trials (SPIRIT guidelines [7, 8].

### Objectives

The aim of the current project is to evaluate the effectiveness and cost-effectiveness of the treatment algorithm for patients with a complete primary ACL rupture compared to current used treatment strategy. We hypothesize that the treatment algorithm will lead to earlier identification of the optimal treatment for the individual patient. We expect that fewer patients will receive a surgical reconstruction compared to the current practice and that fewer patients will need delayed surgery after non-operative treatment has failed. Hence, we hypothesize that with the treatment algorithm faster recovery of functional outcome will be achieved compared to the current practice (superiority study). As secondary outcome we expect that a faster recovery of functional outcome will lead to a faster return to work and sports. Hence, we hypothesize that the treatment algorithm will lead to lower societal cost. The treatment algorithm provides extra information for the physician and as well for the patient, to include in their decision for a(n) (non-)operative treatment. Therefore we expect the treatment algorithm will impact the shared decision making communication process.

#### Primary objective

Assessing whether the treatment algorithm for patients with a complete primary ACL rupture is superior to the current practice regarding recovery of functional outcome at two-year follow-up.

#### Secondary objectives

Assessing whether the treatment algorithm for patients with a complete primary ACL rupture is superior to the current practice regarding recovery of functional outcome during two-year follow-up.Assessing whether this treatment algorithm will increase the cost-effectiveness compared to the current practice.Assessing whether this treatment algorithm will lead to less ACL reconstructions compared to the current practice.Assessing whether this treatment algorithm will extend the (perception of) shared decision making during a physician-patient consultation.

### Study design

The ROTATE-trial is an open-labeled cluster randomized controlled trial with superiority design. It is a multicenter study performed in orthopedic departments of ten hospitals throughout the Netherlands. Of the ten hospitals one is an academic hospital, one a private clinic and eight are general hospitals. In all participating hospitals, the local responsible authorities approved the conduct of the study. The study protocol was approved by the Erasmus MC Ethics Committee and was registered in the Dutch Trial Registry. (Registration number: NL8637).

### Recruitment procedures

All adults with an ACL rupture, visiting an orthopedic surgeon of one of the participating hospitals, who meet the eligibility criteria will be invited to participate. These patients receive the participant information sheet and will have sufficient amount of time to decide upon participation. Written informed consent is obtained from the patient prior to inclusion. At inclusion, the patient and physician will come to a treatment preference dependent on which treatment decision strategy they will use.

### Inclusion criteria

In order to be eligible to participate in this study, a subject must meet all the following criteria: aged 18 year or older, with a complete primary ACL rupture (confirmed by magnetic resonance imaging (MRI) and physical examination), maximum of 6 weeks of non-operative treatment, and willing to comply with the study protocol.

### Exclusion criteria

A potential subject who meets any of the following criteria will be excluded from participation in this study: multi ligament trauma indicated for surgical intervention (eg. every multi ligament trauma besides medial collateral injury combined with an ACL rupture), presence of another disorder that affects the activity level of the lower limb (such as lateral/posterolateral ligament complex with significantly increased laxity, general systemic disease affecting physical function or any other condition or treatment interfering with the completion of the trial, including patients with metal devices or motion disorders), pregnancy, and insufficient command of the Dutch language.

### Randomization

To avoid dilution between both treatment decision strategies, randomization will take place on hospital level. This means that the treatment choice of all patients referred by one hospital will be based on the same treatment decision strategy. This will be done to overcome that the treatment choice of a participating orthopedic surgeon is influenced by knowledge of the algorithm, in case the patient is assigned to the control group. Secondly, this will be done to overcome logistic difficulties such as switching back and forth between different treatment decision strategies. Randomization will take place when institutional review board acceptance has been obtained, and will be executed by the use of a computer generated randomization list.

### Algorithm development

A treatment algorithm has been formulated based on current literature, results of the COMPARE study, and finalized by an expert group consisting of orthopaedic surgeons and researchers specialized in traumatic knee injuries [2]. Disagreements on the contents of the algorithm were resolved by consensus. This algorithm generates an advice which patients have a high probability that they a) will not respond to an exercise program under supervision of a physical therapist, and are therefore indicated for early surgical reconstruction and b) will respond to an exercise program. The algorithm application will be used in the shared decision process to come to a personalized treatment choice.

### Intervention group

At the initial consult, the ACL rupture will be clinically diagnosed. Additional patient specific information will be collected essential for the ACL treatment algorithm. The patient will be referred to the radiology department for an MRI of the affected knee. During the second consultation the physician and patient come to a shared treatment plan for treating ACL rupture based on multiple determinants, including an advice from the treatment algorithm. To ensure study methodological safety and because the ROTATE-trial is still including patients we can’t disclose what other determinants are added in the adjusted treatment decision strategy. The adjusted treatment decision strategy is visualized in Fig. 1.

**Fig. 1 Fig1:**
[figure not shown]
Flowchart adjusted treatment decision strategy intervention group. MRI, magnetic resonance imaging; ACL, anterior cruciate ligament; OR, operating room

### Control group

Usual care in which the treatment decision is made based upon the experience of the orthopedic surgeon combined with the preference of the patient.

### Measurements

Patients will be asked to fill in questionnaires at baseline, 3, 6, 12, and 24 months. Knee specific physical examination, based on the International Knee Documentation Committee (IKDC) examination form, will be performed at baseline, 12 and 24 months. Physical examination consists of the following: passive range of motion, presence of effusion, valgus / varus stress test, Lachman test, anterior drawer and pivot shift test. In each participating hospital the knee specific physical examination will be performed by an orthopedic surgeon or an assessor trained by the coordinating researcher.

### Shared decision making process

In this study, specific attention is given to shared decision making. This takes into account that not only the outcome of the decision is important (determination), but also the process of coming to a decision (deliberation) [9, 10].

The shared decision making process will be evaluated from the perspective of the patient and the physician. Patients will be asked for their treatment preference three times, as explained above in the description from the intervention group. Through this we can measure the patients preference before and after the intervention. After the second consult, the decisional process on patient level is measured by a questionnaire. In addition, the treatment preference of the physician is recorded for this study, without disclosing this information to the patient. The physician is allowed to share his or her treatment preference after the advice from the algorithm is given. The decisional process on physician level is measured qualitatively through focus groups in each participating center. For these sessions, which will be chaired by the researcher of the coordinating center, the surgeon specialized in treating ACL ruptures will be invited. In case only one physician participates in the study, an individual interview will be conducted instead. The focus groups will be conducted twice in the intervention group centers and once in the control group centers, unless there has been a change in treatment protocol in one of the control group centers. Focus groups/interviews will be audio recorded with permission. Patients’ and physicians’ remarks or scores on the shared decision making process will be evaluated and compared between intervention and control group centers.

## Outcomes

### Primary outcome

The primary outcome is the difference between both groups in patients’ perception of symptoms, knee function and ability to participate in sports activities assessed by IKDC questionnaire at 24 months follow-up. A higher IKDC score reflects more favourable patients’ ratings of symptoms, knee function, and ability to participate in sports activities (optimal score is 100). The IKDC is a valid and responsive (ability to detect changes in time) outcome measure for patients with an ACL rupture [11].

### Secondary outcomes

At baseline we will collect the following baseline characteristics, age, sex, height, weight, educational level, smoking habit, side affected and date and kinetics of trauma. Patient-rated outcome measures (PROMs) will be sent online at baseline, 3, 6, 12 and 24 months. There is an overview of all PROMs per follow-up moment in Table 1.

**Table 1 Tab1:** Patient-rated outcome measures (PROM) per follow-up moment

*PROMs*	*Baseline/1st consult*	*3 months*	*6 months*	*12 months*	*24 months*
*IKDC - subjective*	*x*	*x*	*x*	*x*	*x*
*Tegner*	*x*	*x*	*x*	*x*	*x*
*KOOS*	*x*				*x*
*Lysholm*	*x*	*x*	*x*	*x*	*x*
*NRS*	*x*	*x*	*x*	*x*	*x*
*Tampa scale*	*x*			*x*	*x*
*EQ-5D-5L*	*x*	*x*	*x*	*x*	*x*
*SDM-Q-9*	*x*				
*iMCQ/iPCQ*		*x*	*x*	*x*	*x*

*PROM* patient-rated outcome measures, *IKDC* International Knee Documentation Committee, *KOOS* Knee injury and Osteoarthritis Outcome Score, *NRS* number rating scale, *EQ-5D-5L* EuroQol 5D, *SDM-Q-9* 9-ltem Shared Decision Making Questionnaire, *iMCQ* Medical

We will measure the patients’ perception of symptoms, knee function and ability to participate in sports activities at 3, 6 and 12 months follow-up with the IKDC questionnaire. As mentioned above, the 24 month follow-up will be our primary outcome. Work and sports activities will be measured with the Tegner questionnaire (range 0–10; highest activity score is 10) at baseline, 3, 6, 12 and 24 months [12]. The Knee injury and Osteoarthritis Outcome Score (KOOS) will be assessed at baseline and 24 months of the subscales pain, symptoms, ADL, sports and quality of life (QoL) (range 0–100; optimal score is 100) [13]. Knee instability will be measured with the Lysholm questionnaire (range 0–100; optimal score is 100) at baseline, 3, 6, 12 and 24 months [12]. Knee pain will be assessed with the number rating scale (NRS) (range 0–10; optimal score is 0) at baseline, 3, 6, 12 and 24 months. Kinesiophobia will be measured with the Tampa scale at baseline (range 17–68; optimal score is 17), 12 and 24 months [14]. General quality of life will be measured with the EQ-5D-5L questionnaire (range − 0.329 to 1; optimal score is 1) at baseline, 3, 6, 12 and 24 months. EQ-5D-5L use is recommended for the assessment of quality of life in trauma patients, especially for economic assessments. The patients’ EQ-5D-5L health states will be converted into utility scores using the Dutch tariff. The EQ-5D will be used for the cost-utility analysis [15].

Intramural and extramural medical costs will be assessed with the Medical Consumption Questionnaire (iMCQ) and productivity loss will be assessed with the Production Consumption Questionnaire (iPCQ) at 3, 6, 12, and 24 months follow-up. These questionnaires are validated by the Institute of Medical Technology Assessment (Erasmus University, Rotterdam, The Netherlands). iMCQ includes details on medical specialist care, physical therapy, hospitalization, nursing home, home care, and other costs directly associated with diagnosis, treatment and rehabilitation. iPCQ includes details on work resumption and production losses [16].

For patients, the efficacy of the shared decision making process will be evaluated using the score on the 9-ltem Shared Decision Making Questionnaire (SDM-Q-9) that is administered directly after the consultation. The SDM-Q-9 is a patient-reported measure that focuses on the decisional process by rating physicians’ and patients’ behavior in medical encounters [17]. The aggregated scores over all items of the SMD-Q-9 lead to a total raw score between 0 and 45, with 0 indicating the lowest and 45 indicating the highest level of perceived shared decision making.

For physicians, the efficacy of the shared decision making process will be evaluated at one or two time points, at the start of the inclusion period prior to the first inclusion in intervention and control centers and at the end of the inclusion period after the last inclusion in intervention centers. This will be evaluated using interviews/focus groups. The proposed topic lists are based on the SDM-Q-9-Doc questionnaire (the physician version of the SDM-Q-9) and the Technology Acceptance Model (TAM) [18]. Every interview/focus group session will be analyzed qualitatively and compared between control and intervention centers. After the inclusion period, we will analyze whether there is an improvement of perceived shared decision making when using our treatment algorithm.

Physical examination of the knee will be assessed by the objective IKDC questionnaire at baseline, 12 and 24 months. (Table 2) Information about the received treatment is reported including the surgeons fidelity to the intervention. We address the number of patients that cross over from their allocated treatment. (Serious) Adverse events ((S)AE’s) are noted.

**Table 2 Tab2:** Measurements per follow up moment

	*Baseline*	*3 months*	*6 months*	*12 months*	*24 months*
*Physical examination*	*x*			*x*	*x*

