#### Secondary outcome

To evaluate the between group difference in course in IKDC scores over the follow-up period, as indicated by the interaction between time point and randomized allocation, we will use mixed models. The IKDC score (at baseline and after 3, 6, 12 and 24 months of follow-up) will be used as a dependent variable. The randomized allocation will be used as an independent variable. Follow-up period and the interaction between follow-up and randomized allocation will be entered into the model as fixed factors.

Difference between groups in knee pain, kinesiophobia, shared decision making for patients and quality of life will be used as secondary outcomes. The analyses will be performed by using linear or binary mixed models for repeated measures. Return to pre-injury sport level, satisfaction with treatment and adverse events will be reported as comparative frequencies. Because of the potential for type 1 error due to multiple comparisons, findings for analyses of secondary endpoints should be interpreted as exploratory.

Difference between groups in shared decision making for physicians will be analyzed qualitatively, using the transcripts of the interviews’/focus groups’ audio files. The coding process will result in themes and patterns of shared meaning, underpinned or united by a central concept which are important for our research question [19].

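### Table 1 puts the only SDM-Q-9 measurement at the first consult, while the text puts it after the second, where the algorithm's advice enters the decision

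*Protocol article*

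**What the plan says.** Four parts of the protocol article bear on when SDM-Q-9 is completed.

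- **Secondary outcomes, Table 1:** SDM-Q-9 is marked once, under "Baseline/1st consult". The cells for 3, 6, 12 and 24 months are empty.
- **Shared decision making process:** "After the second consult, the decisional process on patient level is measured by a questionnaire".
- **Secondary outcomes, text:** "The SDM-Q-9 is a patient-reported measure that focuses on the decisional process", and it is a questionnaire "that is administered directly after the consultation". Which consultation is not stated.
- **Intervention group:** "At the initial consult, the ACL rupture will be clinically diagnosed". The inputs for the algorithm are also collected then, and the patient is referred for MRI. After that: "During the second consultation the physician and patient come to a shared treatment plan for treating ACL rupture based on multiple determinants", one of these being the algorithm's advice.

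The Control group section describes usual care and gives no sequence of consultations.

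On analysis, the Secondary outcome part of Data analysis lists patient-level shared decision making with knee pain, kinesiophobia and quality of life, and says of all four: "The analyses will be performed by using linear or binary mixed models for repeated measures".

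**The concern.** The table and the text give different time points for the same measurement, and they fall on opposite sides of the intervention. A score taken after the first consult precedes the algorithm's advice. A score taken after the second follows it.

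The fourth secondary objective asks whether the algorithm extends perceived shared decision making during the consultation, and shared decision making is in the trial's title. SDM-Q-9 is the only scored patient measure for that objective; the physician side is assessed qualitatively. It is scheduled once, so a score taken at the wrong consultation cannot be replaced by one from a later visit.

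A smaller misfit is that an outcome with one value per patient is grouped with repeated outcomes under a repeated-measures model.

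**Working it through.** The plan states no figure on this point, so there is nothing to reproduce. The check compares sections and counts measurement occasions.

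**1. Is the questionnaire in the process section SDM-Q-9?** That section does not name it. It says that a questionnaire measures the decisional process at patient level. The outcomes text describes SDM-Q-9 as the patient-reported measure of that process, and no other such instrument appears in the article. The identification is an inference, but a safe one.

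**2. The time points side by side**

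| Source in the protocol article | Time of SDM-Q-9 |
|---|---|
| Table 1 | Baseline, first consult |
| Shared decision making process | After the second consult |
| Secondary outcomes, text | Directly after a consultation, not specified |

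The first two cannot both be right as written, and the third fits either.

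**3. Where the intervention falls.** In the intervention arm the order is: first consult (diagnosis, algorithm inputs), MRI, second consultation (algorithm advice, shared plan). By the table, SDM-Q-9 comes before the advice. By the process section, it comes after.

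**4. Is there a slot for the text's version?** Table 1 has five columns: baseline/first consult, 3, 6, 12 and 24 months. None is reserved for the second consultation. The first column also holds IKDC, EQ-5D-5L and the other baseline scores, which should precede the treatment decision. SDM-Q-9 has to follow that decision, so one column is serving two different purposes.

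**5. Occasions against the model.** Counting marks in Table 1 for the four outcomes named in the analysis sentence:

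| Outcome | Instrument | Occasions |
|---|---|---|
| Knee pain | NRS | 5 |
| Quality of life | EQ-5D-5L | 5 |
| Kinesiophobia | Tampa scale | 3 |
| Shared decision making | SDM-Q-9 | 1 |

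With one score per patient there is no time term, no time-by-group term and no within-patient correlation to estimate. What remains, for patient i in hospital j, is

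score(ij) = b0 + b1 × arm(j) + u(j) + e(ij),

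with u(j) the random hospital effect. This is the structure already given for the primary outcome, without the baseline covariate. A between-group comparison does not need a baseline SDM-Q-9 value.

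**The case against.** The strongest reply is that the text already shows the intent and the header is only a loose label. The process section names the second consult, and the intervention section puts the shared plan there. Table 1 has no column between baseline and 3 months, so anything measured around the decision would have to go in the first. The baseline period may well run to the decision visit: eligibility requires MRI confirmation, MRI follows the first consult, and the recruitment section has patient and physician reach a treatment preference at inclusion. This largely stands as an account of what was probably meant. It does not remove the contradiction, because the header names the first consult and the outcomes text leaves the consultation open.

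Three stronger readings are tempting, and the documents support none of them.

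- **The algorithm's effect on SDM-Q-9 would be zero by construction.** Only the effect of the advice itself is ruled out at the first consult. The trial is open-label and intervention physicians already collect algorithm inputs at that visit, so perceived behaviour could differ between arms then. Any percentage loss of effect would simply restate an assumed share of mistimed questionnaires; the article gives none.
- **Timing would vary by hospital and so be confounded with arm.** Randomising ten hospitals makes this conceivable, but nothing shows that hospitals set the timing themselves. The questionnaires are sent online and managed in one data-capture system, and the article does not say that its table was the specification for that system.
- **The mixed model is impossible.** Only the repeated-measures label fails to fit. With one score per patient the model reduces to the hospital random-effect form above.

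**Conclusion.** The contradiction holds: Table 1 and the process section place the single SDM-Q-9 measurement at different consultations, and the outcomes text does not decide between them. If the table were followed, the score would precede the algorithm's advice and could not reflect it.

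The size cannot be given. Anywhere from none to all of the SDM-Q-9 scores could be mistimed, and a pure labelling error, with none mistimed, is quite plausible. The conclusion assumes that the unnamed questionnaire in the process section is SDM-Q-9 and that the second consultation is where treatment is decided. The article describes that pathway for the intervention arm only, so the matching control time point is also undefined.

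This is worth correcting because the measure is the only scored patient evidence for a stated objective. It is not a threat to the trial's main result: the secondary endpoints are declared exploratory, and the primary IKDC analysis does not depend on it. The model wording is a minor point.

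**What to change.** 1. Reconcile Table 1 with the process section and the outcomes text. Give SDM-Q-9 its own time point, directly after the consultation in which the treatment decision is made.
2. Define that time point by the decision rather than by visit number, and in the same way in both arms, since no consult sequence is described for controls.
3. Record the completion date and the date of the decision consultation. The trial was still recruiting when the article was written, so changing the schedule would not repair any score already taken too early. The dates would let such scores be identified and handled separately.
4. In the secondary analysis text, exempt SDM-Q-9 from the repeated-measures wording and specify a single-time linear mixed model with allocation as fixed effect and hospital as random factor.

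The cost is a table edit, one sentence of analysis text and, if the system does follow the table, one changed trigger in the data-capture tool. No questionnaire is added and the burden on patients does not change.
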